### Participants

#### Sample Size

A minimal sample size of 10 participants per group is recommended in pilot studies [25,26]. Because studies with repeated measures (such as crossover designs) require more time commitment from participants (ie, multiple measurements over time), an attrition rate of approximately 15% (n=2 per group) can be anticipated, which is consistent with what has been reported in previous studies conducted in the targeted population [27,28]. To account for this, the recruited sample size was estimated to be 12 participants per group.

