#### Patients

A sample size of 24 patients is targeted, with 12 being able to self-report and 12 unable to self-report. Patients able to self-report will be asked about their music preferences, levels of pain intensity, distress, and acceptability of the POMI.

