#### Preliminary Efficacy of POMI on Acute Pain

Pain will be assessed at 4 different timepoints for each intervention period: before the intervention, immediately after the intervention, during the bed turning procedure, and 30 minutes after the bed turning procedure (Figure 1, T_0_-T_3_). Pain assessments will be performed using validated tools as recommended in ICU clinical practice guidelines [1]. For all patient participants, the CPOT will be used because it is one of the most valid behavioral scales for assessing pain in critically ill adults [42]. In addition to the CPOT, patient participants able to self-report will be asked to rate their pain intensity using the 0-10 Faces Pain Thermometer [43] and their pain distress on a 0-10 NRS [44,45].

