#### Feasibility of Research Methods

Descriptive statistics will be generated for each of the feasibility of research methods items. The screening and recruitment procedures will be described and include the number of patients screened, the proportion of eligible patients as well as the number of enrolled participants. If less than 50% of the potential patient participants are found to be eligible, considerations will be made to broaden the inclusion criteria in an eventual full-scale RCT [39]. Time to recruit will be considered adequate if 24 patient participants are enrolled within 6 months. All issues related to recruitment will be described and grouped into categories by the student researcher.

The retention rates will be calculated and expected to be above 80%. Reasons for participant withdrawal will be described, when known, and if retention rates are below 80%, strategies will be recommended to reduce attrition, based on the reasons for study withdrawal. If more than 10% of the participants (in each group) are found to have missing data, reasons for missing data will be described to inform how to reduce the amount of missing data in future research.

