#### Preliminary Efficacy

Descriptive statistics will be computed for all outcomes (CPOT, pain intensity, and pain distress scores). The 95% CIs will be computed for each dependent variable at each time point.

Considering the small sample size for a pilot study, the potential efficacy of the POMI will be analyzed using nonparametric tests. For the dependent variables (CPOT, pain intensity, and pain distress scores), the Friedman test will be used to compare the scores at individual time points in each group separately. If the Friedman test is found to tend toward significant (*P*<.10), the Wilcoxon signed rank test will be used to compare 2 timepoints in pairs with a Bonferroni correction (.05 per number of tests) to locate the differences.

The preliminary efficacy findings will not be used to inform the decision to pursue a full-scale RCT. However, any tendency toward statistical significance (*P*<.10) or significant lower pain scores in the music period versus the control period will support that the intervention group might decrease pain over time, compared to the control group. A formal hypothesis of efficacy will need to be tested in a full-scale RCT, which will only be recommended if the POMI is deemed acceptable and feasible.

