### Ethics Approval

Ethics approval was submitted in July 2021 and approved in December 2021 (Project #2022-3005). Participation in this research project is voluntary and ongoing for all participants. Participants are free to refuse to participate and may withdraw from this research study at any time, without having to give a reason, and without any consequence to them now or in the future. The participant’s decision not to participate in the study, or to withdraw from it, will have no impact on the quality of care and services to which they are otherwise entitled. Participants are free to refuse to answer any question and remain in the study. Participants are free to refuse to be video recorded.

For a patient who is unable to consent to participate in the study, a family member representative will provide the written consent on behalf of the patient. From this time and until the patient participant is discharged from the ICU, the student researcher will follow up on the ICU adult patients who were unable to consent to determine if they regain the ability to consent for themselves. In the case where a patient participant who was previously unable to consent regains the ability to consent at any time, before or after the intervention, the student researcher will present the research project and the information and consent form to allow the ICU adult patient to make an informed decision regarding their participation in the study.

The data collected from a participant as part of this study, excluding the video recordings, could be used for future research projects related to this study only with the participant’s explicit permission. The results of the research study, excluding video recordings, may be presented at conferences, published in specialized journals or be the subject of scientific discussions, or be used for teaching purposes. No identifying information will be published in any way.

At any time, participants have the right to consult their study file in order to verify the information gathered and to have it corrected if necessary. All study data will be stored safely for 10 years, after which time they will be permanently destroyed by being either shredded or permanently deleted from the server.

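### Minor: one skipped self-report rating removes that patient's period from the Friedman test, and the 12-per-group size allows for withdrawals only

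*Protocol article*

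**What the plan says.** On measurement (Preliminary Efficacy of POMI on Acute Pain): "Pain will be assessed at 4 different timepoints for each intervention period". The CPOT, a behavioral scale, is scored in all patients. Pain intensity and pain distress are rated only by patients able to self-report.

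On analysis (Data Analysis, Preliminary Efficacy): "the Friedman test will be used to compare the scores at individual time points in each group separately". Pairwise Wilcoxon signed rank tests follow if the Friedman P value is below .10. Descriptive statistics and 95% CIs are also planned at each time point. Lower scores under music than under control would be read as support for the intervention.

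On size (Sample Size): "A minimal sample size of 10 participants per group is recommended in pilot studies", and "an attrition rate of approximately 15% (n=2 per group) can be anticipated", so "the recruited sample size was estimated to be 12 participants per group". The Patients section gives the strata: "A sample size of 24 patients is targeted, with 12 being able to self-report and 12 unable to self-report".

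On missing answers (Ethics Approval): "Participants are free to refuse to answer any question and remain in the study". The planned response (Feasibility of Research Methods) has a threshold: "If more than 10% of the participants (in each group) are found to have missing data", the reasons will be described.

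**The concern.** The Friedman test ranks the four scores within each patient, so a patient with three of the four cannot enter. The plan expressly permits that situation, because declining a question is not withdrawal. The margin in the sample size is justified by attrition alone.

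Two things follow for pain intensity and pain distress. First, the omnibus test leaves out scores that were collected, in strata that are already small. Second, if blocks are formed separately for the music and control periods, a patient can be complete in one and incomplete in the other. The two tests then describe different sets of patients, although the Discussion counts it as a strength of the crossover that each patient is their own control.

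**Working it through.** **Inputs.** Recommended minimum 10 per group, attrition about 15% (2 per group), 12 recruited per group (Sample Size); 12 patients able to self-report (Patients); 4 ratings per period. The share of ratings missed, q, is not in the document. I assume 2%, 5% and 10%, with misses independent of one another.

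**1. The plan's own figure.** 10 / (1 − 0.15) = 11.8, rounded up to 12. This reproduces the stated 12. Two of 12 is 16.7%, consistent with about 15%. The whole margin is used by the two withdrawals.

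**2. Behaviour of the test.** With 12 patients × 4 scores = 48 simulated scores and one deleted, the Friedman routine in scipy returned no result. It ran only after that patient's row was removed, on 11 patients.

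**3. Complete blocks left, for one self-report outcome in one period.**

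| Incomplete patients | 12 retained | 11 retained | 10 retained |
|---|---|---|---|
| 0 | 12 | 11 | 10 |
| 1 | 11 | 10 | 9 |
| 2 | 10 | 9 | 8 |
| 3 | 9 | 8 | 7 |

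One incomplete patient goes below 10 only when both withdrawals have occurred. With full retention it takes three. One of 10 is exactly 10%, which does not exceed the plan's threshold for describing reasons.

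**4. Size under assumed rates.** A period is complete with probability (1 − q)^4. With 10 retained, the chance of fewer than 10 complete blocks is 1 − (1 − q)^40. With 12 retained, it is the binomial probability of at most 9 complete out of 12.

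| q | Complete | Incomplete | Expected complete of 10 | P(<10), 10 retained | P(<10), 12 retained |
|---|---|---|---|---|---|
| 2% | 92.2% | 7.8% | 9.2 | 55.4% | 6.1% |
| 5% | 81.5% | 18.5% | 8.1 | 87.1% | 39.0% |
| 10% | 65.6% | 34.4% | 6.6 | 98.5% | 83.8% |

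If misses cluster in the same patients, fewer periods are incomplete than shown for a given q.

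**5. A paired comparison at one time point.** This needs two scores, one per condition, so it keeps (1 − q)^2 of patients: 96.0%, 90.3% and 81.0%, or 9.6, 9.0 and 8.1 of 10. If changes from T0 are compared instead, four scores are needed (two per period) and the share falls back to (1 − q)^4, as in step 4.

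**The case against.** The strongest reply is that the handling of incomplete blocks is commonly left to an analysis plan or full protocol that is not shown, and that a right to skip questions does not contradict a complete-block test. That stands: the absence of a missing-data rule is not the point here. What remains is a named test that does not suit partial data the plan allows.

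Several other limits also stand:

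- Declining a question cannot remove a CPOT score, which does not depend on the patient answering. The unable-to-self-report stratum is untouched by this route.
- The loss is confined to the omnibus test for one outcome and period. The descriptive statistics and CIs at each time point use all available scores, and a pairwise Wilcoxon test needs only its two time points.
- The 10 is a general recommendation for pilot size, not a minimum number of Friedman blocks.
- The analysis section does not define group; the Discussion speaks of subgroups. If all 24 patients were pooled per period, one miss would leave 23 (19 of 20 retained) and 10 would not be at risk from a few misses. That pool exists only for the CPOT, since intensity and distress are planned in the 12 able to self-report.
- The article says that the efficacy findings will not decide whether a full trial is pursued, and learning how much is missing is itself a feasibility aim.

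A reader might infer that a single missed rating by itself takes the analysis below 10. It does not: with all 12 retained it leaves 11. A reader might also infer that dropped patients are those in most pain during the turn, so that the remaining scores are biased downwards. The document gives nothing on who misses ratings or when. If it were so, a comparison at that time point would lose the same patients, so the fix below would not cure it.

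**Conclusion.** The point holds in a limited form and is minor. For pain intensity and distress, the Friedman test excludes any patient-period with a skipped rating, and separate tests by condition can then rest on different patients. The sample-size margin covers withdrawals only, so at the planned retention of 10 in the self-report stratum, one incomplete patient gives 9 complete blocks.

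The counts rest on a stratum of 12 as the unit of analysis. The percentages rest on assumed, independent missing rates and show a range, not a forecast. What makes a change worthwhile is less the figure of 10 than the contrast itself: the plan intends to interpret music against control, and a paired comparison delivers that on more of the available scores.

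**What to change.** At each time point, compare music with control within patient by the Wilcoxon signed rank test, in all patients with both scores, and report n per time point. Changes from T0 may be used instead, but they need the T0 scores of both periods as well and so keep fewer patients. Report missed ratings by time point and condition, which also serves the feasibility objective.

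If an omnibus test over T0 to T3 is kept, state its complete-block n for each outcome and period, or use a version that accepts incomplete blocks (Skillings-Mack). A mixed model on all available scores would also use partial data, but it sets aside the plan's small-sample reason for nonparametric tests, so it is a trade-off and not a clear gain.

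Cost: analysis wording only, with no new data. The number analysed will vary slightly between time points.

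### Any uncorrected P<.10 for music versus control counts as support for the music intervention, with no outcome, time point, subgroup or between-period test named

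*Protocol article*

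**What the plan says.** All of the following is in the protocol article.

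- **Timing and outcomes** (Outcomes, Preliminary Efficacy of POMI on Acute Pain): "Pain will be assessed at 4 different timepoints for each intervention period". One assessment precedes the intervention and three follow it. CPOT is scored in every patient. Pain intensity and pain distress are added only for patients able to self-report.
- **Tests** (Data Analysis, Preliminary Efficacy): "the Friedman test will be used to compare the scores at individual time points in each group separately". If that test gives P<.10, signed rank tests compare pairs of time points, "with a Bonferroni correction (.05 per number of tests) to locate the differences".
- **Interpretation** (same section): the trigger is "any tendency toward statistical significance", set at P<.10, or else significantly less pain under music than under control. Either kind of result, the article states, "will support that the intervention group might decrease pain over time, compared to the control group".
- **Limits on use** (same section): the efficacy findings do not feed the decision on a full-scale trial, and a formal efficacy hypothesis is left to that trial.
- **Subgroups** (Methodological Limitations and Mitigation Strategies): the pain data are analysed by subgroup. The tests named there are meant to evaluate the time effect.

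**The concern.** The interpretation sentence is the only rule in the article for reading the secondary efficacy objective. It accepts any result below .10, and nothing limits how many results may be inspected. The section is careful about multiplicity when it asks at which time points scores differ, but applies no such care to the question readers will ask, which is whether pain is lower with music than without. No test for that question is named either.

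The stake is the pilot's efficacy statement. A rule that is often met when music has no effect tells the reader little. It also sits badly with the plan's own position that efficacy needs a formal test in a larger trial.

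**Working it through.** **The plan's own figures.** The article gives no error rate for the P<.10 rule, so there is none to reproduce. Its sample size does reproduce: 10 per group with 15% attrition gives 10 / (1 − 0.15) = 11.76, rounded up to 12. The checks below use 12 per subgroup as recruited and 10 after attrition.

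**Number of comparisons (inferred).** The article does not list its music versus control comparisons. Its outcomes give:

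- CPOT in two subgroups, plus intensity and distress in one: 2 + 1 + 1 = 4 sets.
- Three post-intervention times: 4 × 3 = 12 comparisons. Including T0 would give 16.

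**Level per comparison.** Sidedness is not stated. A two-sided P<.10 that must also favour music has probability .05 under no effect. A P<.10 in either direction has probability .10, as does a one-sided P<.10 in favour of music.

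**Chance of at least one hit under no effect.** For independent comparisons this is 1 − (1 − level)^12. The article gives no correlation, so a range of 0 to 0.8 was assumed. For each setting, 20,000 null trials were simulated with exact signed rank tests on normally distributed within-patient differences, with 12 or 10 patients per subgroup.

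| What counts | Level | Independent | Simulated |
|---|---|---|---|
| Two-sided P<.10, lower pain with music | .05 | 1 − 0.95^12 = 0.46 | 0.23 to 0.43 |
| P<.10 in either direction | .10 | 1 − 0.9^12 = 0.72 | 0.43 to 0.69 |
| Bonferroni, .05/12 | .0042 | 1 − (1 − .05/12)^12 = 0.049 | 0.030 to 0.049 |

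The simulated values at zero correlation fall slightly below the formula because the exact test is discrete. At n=12 the attained one-tailed level is 0.046, and 1 − (1 − 0.046)^12 = 0.43.

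**Sensitivity to the count.** With 16 comparisons the directional figure is 1 − 0.95^16 = 0.56 if independent, and 0.26 to 0.53 in simulation. Passing one half takes at least 7 independent comparisons at .10 (1 − 0.9^7 = 0.52) or 14 at .05 (1 − 0.95^14 = 0.51).

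**The case against.** The strongest reply is that little depends on this sentence. Efficacy is a secondary and preliminary objective, the conclusion is hedged, and progression rests on acceptability and feasibility. That stands, and it limits the consequence to reporting. It does not make the rule informative.

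It can also be said that the count of 12 is a construction. That stands too, so the figures are conditional on it. The count nevertheless follows from the article's own outcomes, subgroups and time points, and the open-ended rule is what leaves the number unfixed.

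A reader might go further in three ways that the article does not support:

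- **That the P<.10 rule cancels the Bonferroni correction.** The correction concerns pairs of time points and the P<.10 sentence concerns music against control. For six pairs the corrected level is .05/6 = .0083, but setting that beside .10 compares thresholds for different questions. The correction stays in force where it was placed. The fault is that it goes no further.
- **That false support is more likely than not.** The wording leaves the direction of a tendency loose, but a result showing more pain with music could hardly support a decrease. On the natural two-sided, directional reading, every figure for 12 comparisons is below one half. One half is passed only if direction is ignored or the test is one-sided at .10, and then not at every correlation. It is also passed if T0 is counted and the comparisons are nearly independent. Repeated scores from the same patients are likely to be positively correlated, which lowers the figure.
- **That a Friedman P<.10 within the music period would count as support.** Bed turning alone could produce one without any music effect. The sentence, however, refers to the music period against the control period, and the Friedman test does not make that comparison.

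**Conclusion.** The point holds as a fault in the interpretation rule. Under no effect, the rule yields at least one supportive result with probability about 0.23 to 0.46 on the directional two-sided reading and about 0.43 to 0.72 if direction is ignored. Applying the section's own correction to the same comparisons would hold this to about 5% or less.

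These figures assume 12 comparisons, correlation between 0 and 0.8, and 10 to 12 patients per subgroup. The simulated differences have no ties, so real CPOT scores would shift the figures somewhat. That the rule is unadjusted and open-ended is certain from the text. The exact probability is not.

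The decision on a full-scale trial is not affected. What is affected is whether the published efficacy statement can be given any weight.

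**What to change.** Before the pain data are analysed, delete the sentence that ties support to P<.10. Report the within-patient POMI minus CTL differences, by outcome, time point and subgroup, as estimates with 95% CIs. The section already plans CIs for each outcome at each time point, and Methodological Strengths already intends to work out individual differences, so the added work is small.

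If a support statement is kept, do one of the following:

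- Fix one between-period contrast in advance: outcome, time point, population, test and sidedness. CPOT during turning in all 24 patients would be one example, but pooling the subgroups departs from the planned analysis by subgroup and would need to be stated.
- Apply the Bonferroni correction to the full, listed set of music versus control comparisons.

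The cost is a change of wording. The downside is that fewer results can be called promising.

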### Ethics Approval

Ethics approval was submitted in July 2021 and approved in December 2021 (Project #2022-3005). Participation in this research project is voluntary and ongoing for all participants. Participants are free to refuse to participate and may withdraw from this research study at any time, without having to give a reason, and without any consequence to them now or in the future. The participant’s decision not to participate in the study, or to withdraw from it, will have no impact on the quality of care and services to which they are otherwise entitled. Participants are free to refuse to answer any question and remain in the study. Participants are free to refuse to be video recorded.

For a patient who is unable to consent to participate in the study, a family member representative will provide the written consent on behalf of the patient. From this time and until the patient participant is discharged from the ICU, the student researcher will follow up on the ICU adult patients who were unable to consent to determine if they regain the ability to consent for themselves. In the case where a patient participant who was previously unable to consent regains the ability to consent at any time, before or after the intervention, the student researcher will present the research project and the information and consent form to allow the ICU adult patient to make an informed decision regarding their participation in the study.

The data collected from a participant as part of this study, excluding the video recordings, could be used for future research projects related to this study only with the participant’s explicit permission. The results of the research study, excluding video recordings, may be presented at conferences, published in specialized journals or be the subject of scientific discussions, or be used for teaching purposes. No identifying information will be published in any way.

At any time, participants have the right to consult their study file in order to verify the information gathered and to have it corrected if necessary. All study data will be stored safely for 10 years, after which time they will be permanently destroyed by being either shredded or permanently deleted from the server.

Patients and families will be offered the hyperlink to their playlist as well as a paper version of the list of songs played as part of the study. Nursing staff participants will be offered a US $20 gift certificate to compensate for their time spent participating in the study.

